## Sample size calculation

The sample size of this study was calculated by using data from earlier studies [4, 5]. With one control per experimental subject, an accrual interval of 18 months, and additional follow-up after the accrual interval of 12 months, an alpha risk of 5 % and power of 80 %, assuming 30 % SA recurrence in the first year after an SA and median SA recurrence at 3 months, and an estimated hazard ratio of 0.66, we will need 92 subjects in each group. Assuming 10 % lost to follow-up, we will aim to enroll 112 subjects in each group. This sample size was calculated by using Power Sample Size v3.0.43 for Windows.

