### Primary outcome analysis

To identify differences in SA recurrence, a time-to-event analysis with Cox regression modeling will be used. The study period will be up to 12 months after the SA of inclusion. Patients without another SA, who die, or who are lost to follow-up will be censored. Patients with and without an SA during the study period will be compared between the MEDIA and CLASSIC groups. Factors associated with SA recurrence will be compared by log rank test, with *p* < 0.05 considered statistically significant. Cox proportional hazards modelling of SA recurrence will include sex, group and other variables with *p* < 0.2 on univariate analysis (i.e., explanatory variables). The score obtained from the CES-D at the time of inclusion will be considered an explanatory variable. This method will allow for considering a confusion factor and determining which initial characteristics are significant risk factors for recurrence of SA. Hazard ratios (HRs) and 95 % confidence intervals (95 % CIs) will be calculated to indicate the probability of SA recurrence by characteristics entered in the model. We will test for interactions between the included variables. Each variable will be checked for proportionality assumption by a graphical method and the Moreau method, and variables not meeting proportionality will be used for stratification [36].

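### The sample size of 92 per group works only if almost every patient recurs; at the plan's own 30% one-year recurrence, 112 per group gives about 35% power, not 80%

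*Protocol article*

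**What the plan says.** The section on sample size calculation in the protocol article gives these inputs: 1:1 allocation, 18 months of accrual, "additional follow-up after the accrual interval of 12 months", alpha 5%, power 80%, and 30% "SA recurrence in the first year after an SA and median SA recurrence at 3 months, and an estimated hazard ratio of 0.66". The result is 92 patients per group. With 10% lost to follow-up, the enrolment target is 112 per group, 224 in all.

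The section on the primary outcome analysis sets a different horizon: "The study period will be up to 12 months after the SA of inclusion". Patients without a further attempt are censored, so only recurrences count as events. The 30% is the article's working figure throughout: the abstract gives about 30%, and the background gives almost one third within a year.

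**The concern.** A time-to-event comparison draws its power from the number of events. If 30% of controls recur within a year, the median time to recurrence for the whole group is not reached in 12 months. If the median for the whole group is 3 months, half recur by month 3 and, with a constant hazard, 1 − 0.5^4 = 94% by month 12. Both figures cannot describe the same group of patients, and which one drove the calculation decides the number of events.

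The statistical method section calls the primary analysis confirmatory. If the near-universal recurrence was used, the trial has far fewer events than its stated power requires. A null result could then be read as evidence that text messages do not prevent recurrence, when the study had about one chance in three of detecting its own target effect.

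**Working it through.** **Inputs.** Hazard ratio 0.66, alpha 5% (taken as two-sided; the article does not say), power 80%, 1:1 allocation, 30% one-year recurrence (taken as the control rate), 3-month median, 18 months of accrual plus 12 months of additional follow-up, 92 and then 112 per group, 10% loss: all from the sample size section. The 12-month analysis horizon is from the primary outcome section.

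**1. Events required (Schoenfeld).**
4 × (1.960 + 0.842)² / (ln 0.66)² = 181.8, so 182 events. Against 2 × 92 = 184 patients this is 181.8 / 184 = 98.8% recurring.

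**2. Reproducing the plan's 92.** Assume exponential recurrence with a 3-month median for all patients and uniform accrual over A = 18 months with F = 12 months more. With λ = ln 2 / median, the event probability is
1 − (e^(−λF) − e^(−λ(A+F))) / (λA).

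| Medians in the two groups (months) | Event probabilities | n per group |
|---|---|---|
| 3 and 3 × 0.66 = 1.98 | 98.5%, 99.8% | 91.7, i.e. 92 |
| 3 and 3 / 0.66 = 4.55 | 98.5%, 94.5% | 94.2 |

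The first row matches exactly; the second is within 3% before rounding up. The 30% enters neither.

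**3. Events and power at 30% by 12 months.** Under proportional hazards the rate in the MEDIA group is 1 − 0.70^0.66 = 21.0%. Events = n × (0.300 + 0.210). Power = Φ(0.4155 × √events / 2 − 1.960).

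| Patients per group | Events | Power |
|---|---|---|
| 92 | 46.9 | 29.6% |
| 100.8 (112 less 10%, lost patients contributing nothing) | 51.4 | 31.9% |
| 112, no loss | 57.1 | 34.8% |

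For 112 without loss, the Freedman formula and a comparison of two proportions each give 34.0%. A simulated log-rank test (6,000 runs) gives 34.6%, or 33.7% with 10% loss when lost patients count until they leave.

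**4. What 80% power would take.** 182 / 0.5097 = 357 per group, or about 397 if 10% are lost and contribute nothing. With 112 per group and no loss, 80% power is reached only at a hazard ratio of about 0.45 (30% against about 15%). With 100.8 per group it is about 0.43.

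**5. Sensitivity, 112 per group without loss.**

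| Change of reading | Power |
|---|---|
| Control recurrence 20% / 50% at 12 months | 25% / 53% |
| 30% read as the pooled rate (67 events) | 40% |
| One-sided 5% | 47% |
| 0.66 read as a risk ratio (30% against 19.8%) | 34% (Schoenfeld) to 42% (two proportions) |
| Follow-up of 12 to 30 months at constant hazard (event probabilities 45.8% and 33.4%) | 50% |

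**The case against.** The strongest reply is that the two inputs need not conflict. The words "median SA recurrence at 3 months" can mean the median time among patients who do recur, which is compatible with 30% at one year. As a reading of the sentence this is fair, and probably what the source data showed. It does not rescue the result. The 92 is recovered only when the median is applied to everyone, and under the compatible reading the 12-month event count, and so the 35%, is unchanged.

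It can also be said that how the error arose is inferred. The article names the software but not what was typed into it, and the exact match to 92 needs the group with hazard ratio 0.66 to be the one with the 3-month median, so that the other recurs faster. With the hazard ratio in the intended direction the result is 94.2. That stands: the reproduction is strong evidence of the mechanism, not proof. The shortfall does not depend on it, because 182 events cannot come from 184 patients of whom 30% or fewer recur.

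The sidedness of alpha and the meaning of the 30% are not stated, and 35% rests on the usual readings of both. The alternatives move the figure to 40% or 47%. The mismatch in follow-up is real but secondary: with the 3-month median kept and the hazard ratio in the intended direction, a fixed 12 months raises n only from about 94 to about 102 per group.

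Finally, 112 is more than 10% loss requires (92 / 0.9 = 102.2, so 103). The extra patients do not restore the power.

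**Conclusion.** The concern holds. On the plan's own 30% one-year recurrence and hazard ratio of 0.66, 112 per group gives about 57 of the 182 events needed, and power of about 35% rather than 80%. With the planned 10% loss it is about 32% to 34%, depending on how long lost patients are followed. These figures assume a two-sided test, 30% as the control rate, proportional hazards and the 12-month horizon. Varying those readings one at a time, with control recurrence from 20% to 50%, gives 25% to 53%; none comes near 80%. Because the stated power of the confirmatory analysis is wrong by this margin, it must be corrected. The ethics section says inclusions had not yet begun, so the correction can precede the data.

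**What to change.** Replace the calculation with one driven by events, on the same 12-month horizon as the primary analysis:

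- State that a hazard ratio of 0.66 needs 182 events for 80% power at two-sided 5%, and that 112 per group are expected to give about 57 by 12 months without loss, or about 51 if 10% are lost and contribute nothing.
- Remove the 3-month median as a survival input. If it is kept as background, say that it is the median among those who recur.
- Remove the follow-up beyond 12 months, which the analysis does not use.
- State the sidedness of alpha and that 30% is the control rate.
- Restate the power of 224 patients: about 35% for a hazard ratio of 0.66 without loss (about 32% to 34% with it), and 80% only for a hazard ratio of about 0.45 (about 0.43 if 10% contribute nothing).
- State that the result will be read from the hazard ratio and its 95% confidence interval, and that non-significance will not be taken as no effect.

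This costs a rewritten section and a less favourable stated power; it needs no extra patients. It does not raise the power. If the trial is to have 80% for a hazard ratio of 0.66, recruitment would have to reach about 357 per group before loss, which is a separate decision for the sponsor.

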## Statistical method

The primary analyses will be conducted on an intent-to-treat basis with data for all randomised participants. A per-protocol analysis of the primary outcome, adjusted on center, will also be reported. Continuous variables will be described with mean (SD) or median (range) and categorical variables with number (%), as appropriate. The chi-square or Fisher exact test will be used for analysis of qualitative variables and Student *t* or Mann–Whitney test for quantitative variables.

Differences in primary and secondary outcomes between the 2 groups will be tested independently. No formal adjustments will be used to constrain the overall type I error associated with the secondary analyses. Secondary analysis aims to supplement evidence from the confirmatory primary analysis, and results will be interpreted in this context.

Data will by analyzed by using SAS 9.3 for Windows (SAS Inst., Cary, NC). *P* < 0.05 will be considered statistically significant.

### Primary outcome analysis

To identify differences in SA recurrence, a time-to-event analysis with Cox regression modeling will be used. The study period will be up to 12 months after the SA of inclusion. Patients without another SA, who die, or who are lost to follow-up will be censored. Patients with and without an SA during the study period will be compared between the MEDIA and CLASSIC groups. Factors associated with SA recurrence will be compared by log rank test, with *p* < 0.05 considered statistically significant. Cox proportional hazards modelling of SA recurrence will include sex, group and other variables with *p* < 0.2 on univariate analysis (i.e., explanatory variables). The score obtained from the CES-D at the time of inclusion will be considered an explanatory variable. This method will allow for considering a confusion factor and determining which initial characteristics are significant risk factors for recurrence of SA. Hazard ratios (HRs) and 95 % confidence intervals (95 % CIs) will be calculated to indicate the probability of SA recurrence by characteristics entered in the model. We will test for interactions between the included variables. Each variable will be checked for proportionality assumption by a graphical method and the Moreau method, and variables not meeting proportionality will be used for stratification [36].

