## Methods/Design

### Aims and hypothesis

We hypothesized that the SMS sent over a 6-month period after an SA, in addition to usual care, may increase the delay in SA reccurence. Therefore, the primary objective is to determine whether, as compared with usual care, SMS in addition to usual care can be used to keep in touch with adolescent suicide attempters to reduce the delay in recurrence of an SA. A secondary hypothesis is that the SMS received after a first SA will reduce the suicide rate.

Secondary objectives are to determine whether, as compared with usual care, SMS in addition to usual care can be used to keep in touch with adolescent suicide attempters to improve the evolution of 1) their social network, 2) depression and 3) health-related quality of life.

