### Participants and consent

All adolescents receiving treatment after an SA in a pediatric or psychiatric unit of participating hospitals will be eligible for inclusion. An SA is defined as “a non-fatal act in which the individual liberally causes self-injury or ingests a substance in excess of any prescribed or generally recognised therapeutic dosage” [25]. Criteria of inclusion are age 13 to 17 years and receiving treatment for an SA. Informed consent will be obtained from patients and/or their parents. Patients will be excluded if they refuse to give consent, cannot participate (somatic or understandability reasons), are incarcerated, or do not have a cell phone.

Adolescents will be recruited during a psychiatric evaluation within 24 h of admission to the pediatric or psychiatric unit of the participating hospitals.

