### Outcomes

The primary outcome will be the delay of SA recurrence during 12 months after inclusion in the study. The SA recurrence and date of occurrence will be collected by a member of the research team in each participating hospital.

Secondary outcomes will include evaluation and evolution for 6 months after the SA of the adolescent’s social network by using the MSPSS, health-related quality of life by using Kidscreen-27 and VSP-A, and depression by using the CES-D. The scores and their evolution will be compared between CLASSIC and MEDIA groups.

Finally, the entire process will be evaluated by a short self-report at 6 months after the SA.

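### A suicide that is the first suicidal act after inclusion is censored in the primary analysis and enters no listed endpoint; the bias can favour either arm and is probably small

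*Protocol article*

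**What the plan says.** All references are to the protocol article.

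- **Definition of the event.** Participants and consent gives the only definition of an SA, which begins "a non-fatal act in which the individual liberally causes self-injury".
- **Primary outcome.** Outcomes states: "The primary outcome will be the delay of SA recurrence during 12 months after inclusion in the study".
- **Primary analysis.** Primary outcome analysis says that "a time-to-event analysis with Cox regression modeling will be used", sets the horizon with "The study period will be up to 12 months after the SA of inclusion", and gives the censoring rule: "Patients without another SA, who die, or who are lost to follow-up will be censored". The rule makes no distinction by cause of death.
- **Suicide as a hypothesis.** Aims and hypothesis adds: "A secondary hypothesis is that the SMS received after a first SA will reduce the suicide rate".
- **Secondary outcomes.** The list in Outcomes opens with "Secondary outcomes will include evaluation and evolution for 6 months after the SA of the adolescent’s social network by using the MSPSS" and goes on to quality of life and depression. Neither it nor Secondary outcomes analysis mentions suicide or death.

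**The concern.** The event is defined as non-fatal and every death is censored. A patient who survives a second act is therefore a failure, while a patient who dies from the same act leaves the risk set without an event. The most severe form of what the trial tries to prevent is treated like a loss to follow-up.

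This also leaves suicide without a place in the trial's results. The primary endpoint excludes it, the secondary outcomes do not list it, and the stated hypothesis about the suicide rate has no outcome or analysis to answer it. If suicides differed between arms, the primary hazard ratio would be distorted in favour of the arm that had more of them, and no planned comparison would show it.

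**Working it through.** **Step 1: which patients are affected.**

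| Course after inclusion | Handling as written |
|---|---|
| Non-fatal SA, alive at 12 months | Event |
| Non-fatal SA, later suicide | Event, at the earlier SA |
| Suicide with no earlier non-fatal SA | Censored at death |
| Death from another cause | Censored at death |
| No SA to 12 months, or lost | Censored |

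Only the third row is at issue.

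**Step 2: the plan's own figures.** The article gives no number of deaths or suicides, so there is no figure on this point to reproduce. The related figure is 92 per group in Sample size calculation. It can be recovered from HR 0.66, two-sided 5 %, 80 % power, 18 months of accrual plus 12 of follow-up, and exponential medians of 3 and 3 × 0.66 = 1.98 months:

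- d = (1.960 + 0.842)² / (ln 0.66)² = 45.5.
- The event probabilities are 0.985 and 0.998.
- n = 45.5 × (1/0.985 + 1/0.998) = 91.7, so 92 per group, or about 182 events (4d).

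With a second median of 3/0.66 = 4.55 months the same formula gives 94.2. The point here does not depend on this figure. For the illustration I use the same section's 30 % one-year recurrence, which gives far fewer events than 182. If there were more events, each death would weigh less.

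**Step 3: inputs for the illustration.**

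- Followed per arm: 112 × 0.9 = 100.8, taken as 101 (enrolment target and loss from Sample size calculation).
- CLASSIC: 0.30 × 101 = 30.3, taken as 30 events.
- MEDIA at HR 0.66: 1 − 0.70^0.66 = 0.210, and 0.210 × 101 = 21.2, taken as 21 events.
- Suicides as first act: **assumed** 0 to 3, all in one arm. The document supplies no rate.

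**Step 4: effect of counting k suicides as events.** The approximation is HR = ln(1 − p_MEDIA) / ln(1 − p_CLASSIC).

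With k = 0: ln(1 − 21/101) / ln(1 − 30/101) = −0.2331 / −0.3524 = 0.661.

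| k | All in MEDIA: p_MEDIA = (21 + k)/101 | All in CLASSIC: p_CLASSIC = (30 + k)/101 |
|---|---|---|
| 0 | 0.661 | 0.661 |
| 1 | 0.697 | 0.636 |
| 2 | 0.733 | 0.612 |
| 3 | 0.770 | 0.589 |

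Under the written rule the HR stays close to 0.66 in every row. With all 112 per arm and unrounded events (about 57 in total) the results are similar: 0.69, 0.72 and 0.76 if all deaths are in MEDIA; 0.64, 0.62 and 0.60 if all are in CLASSIC. A balanced split nearly cancels. For example, one death in each arm gives ln(1 − 22/101) / ln(1 − 31/101) = −0.2457 / −0.3666 = 0.670.

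**Step 5: comparison with sampling error.**

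- SE(log HR) ≈ √(1/30 + 1/21) = 0.285.
- The 95 % interval around 0.66 is exp(ln 0.66 ± 1.96 × 0.285), about 0.38 to 1.15.
- One death in MEDIA shifts log HR by ln(0.697/0.661) = 0.053, or 0.19 SE. Three shift it by ln(0.770/0.661) = 0.153, or 0.54 SE.
- Three deaths in CLASSIC shift it by ln(0.589/0.661) = −0.115, or 0.40 SE.
- With three deaths counted, the interval is about 0.45 to 1.32 (all in MEDIA) or 0.34 to 1.02 (all in CLASSIC). Both include 1, as does the interval with none counted.

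**The case against.** **Censoring at death is a recognised analysis.** A Cox model that censors at a competing death estimates the cause-specific hazard of non-fatal SA. That quantity is well defined without assuming that the patient who died shared the survivors' later risk. This stands. The fair criticism is that a hazard of non-fatal attempts alone is an incomplete answer when the competing event is suicide and suicide is reported nowhere else.

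**The definition may serve only inclusion.** It sits in the section on participants, where the index act is necessarily non-fatal, and the coding of a fatal re-attempt is inferred, not spelt out. But it is worded as a general definition and is the only one given. Even if fatal acts were meant to count, the rule censoring those who die would contradict that.

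**The article condenses a fuller protocol.** Cause-of-death procedures could well be found there. The point, however, rests on a definition and a censoring rule that the article does state.

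**The numbers are small.** This stands. Suicides may be none, and the shifts for 1 to 3 lie well within sampling error.

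A reader might also draw three stronger conclusions that the documents do not support:

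- *That the rule favours the SMS arm, or always errs in the unsafe direction.* It does so only if MEDIA has more such suicides. If CLASSIC has more, the benefit is understated. Nothing in the article favours either split.
- *That a suicide is credited as 12 event-free months.* The patient leaves the risk set at death, and anyone with an earlier non-fatal SA has already counted as an event.
- *That the rule would overturn the trial's result.* In the illustration the test is non-significant whether or not the deaths are counted.

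**Conclusion.** The concern holds in a limited form and should be fixed. Taken together, the non-fatal definition and the blanket censoring of deaths keep a first-act suicide out of the primary event count. The listed outcomes then leave it out altogether, despite a stated hypothesis about the suicide rate.

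The likely numerical effect is nil to small: no change with no deaths, and roughly 0.02 to 0.04 on the HR per death when all fall in one arm, in either direction. These figures assume 101 followed per arm, 30 % control recurrence at one year, a true HR of 0.66 and at most 3 suicides. The number of suicides is my assumption, not the document's. The case for change rests on the endpoint not matching the trial's question, and only secondarily on the size of the bias.

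**What to change.** 1. In Outcomes and in Primary outcome analysis, define the primary event as the first recurrent suicidal act after inclusion, whether fatal or non-fatal.
2. In the censoring rule, censor only deaths from causes other than suicide.
3. In Aims and hypothesis, replace the suicide-rate hypothesis, which has no matching outcome or analysis, with a descriptive report of the number of suicides by arm.

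Keeping the non-fatal endpoint as primary, with the composite as a sensitivity analysis and suicides reported by arm, would also be defensible. The composite is the more direct answer to the trial's question.

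The cost is a few sentences, plus classification of cause of death for what should be very few cases, preferably without knowledge of allocation. Ethics and permissions indicates that inclusions had not started, so the rule can be settled before any outcome is known.

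### The primary Cox analysis selects its covariates from the data and stands beside an unranked comparison of patients with and without recurrence, which would be biased by unequal loss if done as crude proportions

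*Protocol article*

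**What the plan says.** All places are in the protocol article.

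- **Outcomes** defines the primary outcome as the delay to SA recurrence over 12 months.
- **Primary outcome analysis** opens with Cox regression as the method for finding differences in recurrence. It censors patients who have no further SA, die or are lost.
- The next sentence reads: "Patients with and without an SA during the study period will be compared between the MEDIA and CLASSIC groups". No test, denominator or role is given.
- Then: "Factors associated with SA recurrence will be compared by log rank test", at p < 0.05.
- Then: "Cox proportional hazards modelling of SA recurrence will include sex, group and other variables", the other variables being those with univariate p < 0.2. Baseline CES-D is to be considered as an explanatory variable. Hazard ratios with 95 % CIs are the reported effect measure.
- **Statistical method** assigns chi-square or Fisher tests to qualitative variables and applies p < 0.05 throughout. It waives multiplicity adjustment for secondary analyses only: "Secondary analysis aims to supplement evidence from the confirmatory primary analysis".
- **Secondary outcomes analysis** places a between-group log-rank comparison, for each explanatory variable, among the secondary analyses.

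**The concern.** The article relies on one confirmatory analysis, yet its primary section leaves two things open.

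First, the Cox model is not one model. Apart from sex and group, its content depends on which variables pass a screen in the trial's own data, so the adjusted group hazard ratio is not defined until the data are seen.

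Second, the comparison of patients with and without an SA stands beside the Cox analysis of the same event with nothing to rank them. If it is done as a two-by-two table, follow-up time drops out. A patient lost in month 1 without an SA then counts the same as one followed for 12 months without an SA, which does not fit the censoring rule in the sentence before it.

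If the analyses disagree, a reader cannot tell from the text which one is the trial's answer. If loss differs by arm, the crude comparison is biased.

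**Working it through.** **Inputs from the article (Sample size calculation).** "an alpha risk of 5 % and power of 80" %; "With one control per experimental subject"; hazard ratio 0.66; 112 per group enrolled; 10 % lost. Also "assuming 30 % SA recurrence in the first year after an SA and median SA recurrence at 3 months" and "an accrual interval of 18 months, and additional follow-up after the accrual interval of 12 months". Two-sided testing is assumed, because sidedness is not stated.

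**The plan's own figure.** Events = 4(1.960 + 0.842)² / (ln 0.66)² = 181.8, so 182. With exponential survival, a 3-month control median, the ratio 0.66 applied to the medians, and 18 months of accrual plus 12 of follow-up, the event probabilities are 0.985 and 0.998. Then n = 181.8 / (0.985 + 0.998) = 91.7, so 92 per group. The stated 92 reproduces. The checks below use the 30 % one-year recurrence, because the analysis stops at 12 months.

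**Type I error.** Null trials were simulated with 112 per arm and 30 % recurrence at 12 months. Each had a crude chi-square test (lost patients counted as without an SA), a log-rank test of group, and a Cox model with covariates screened at p < 0.2. The prognostic strengths and the number of candidate covariates are assumptions.

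| Simulation | Loss CLASSIC / MEDIA | Chi-square | Log-rank | Cox | Any of three |
|---|---|---|---|---|---|
| 5,000 trials, 10 candidates (4 prognostic) | 10 % / 10 % | 4.7 % | 4.7 % | 5.2 % | 7.5 % |
| 4,000 trials, sex and CES-D forced in, 6 noise candidates | 10 % / 10 % | 5.2 % | 5.0 % | 5.4 % | 7.7 % |
| as above | 15 % / 5 % | 5.8 % | 5.0 % | 5.0 % | 8.2 % |
| as above | 5 % / 15 % | 5.6 % | 5.3 % | 4.9 % | 8.4 % |

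The simulation error with 4,000 trials is √(0.05 × 0.95 / 4000) = 0.35 points at 5 %. The bound for three independent tests, 1 − 0.95³ = 14.3 %, does not apply, because these tests are highly correlated. In the first simulation with a true HR of 0.66, the three tests did not all agree in about 15 % of trials.

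**Crude proportions.** The control hazard is −ln(0.70)/12 = 0.02972 per month. The MEDIA 12-month risk is 1 − 0.70^0.66 = 0.2097. The true difference is 0.3000 − 0.2097 = 9.0 points.

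*Loss at a constant rate over 12 months.* With event hazard a and loss hazard b, the crude proportion is a/(a + b) × (1 − e^(−12(a + b))).

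- 10 % / 10 %: 28.6 % vs 19.9 %, difference 8.6 points (0.4 lost).
- 15 % CLASSIC / 5 % MEDIA: 27.8 % vs 20.5 %, difference 7.4 points.
- 5 % CLASSIC / 15 % MEDIA: 29.3 % vs 19.4 %, difference 9.9 points.

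(Differences are taken before rounding.) With no true effect, the two unequal patterns give a false difference of 1.5 points, against MEDIA in the first and for MEDIA in the second.

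*Loss spread evenly over the first 6 months, 15 % CLASSIC / 5 % MEDIA.* A lost patient's chance of an SA before loss is 1 − (1 − e^(−6a))/(6a), which is 0.0841 in CLASSIC and 0.0566 in MEDIA.

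- CLASSIC: 0.85 × 0.3000 + 0.15 × 0.0841 = 0.2676.
- MEDIA: 0.95 × 0.2097 + 0.05 × 0.0566 = 0.2021.
- Difference: 6.6 points.

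**The case against.** The strongest reply is that the article already points to Cox. The outcome is a time, the trial is sized on a hazard ratio, Cox opens the primary section, group is always in the model, and one confirmatory primary analysis is mentioned. This stands. A reader might infer that the primary outcome is tested three ways with no confirmatory test at all, and the text does not support that. The log-rank test is tied to factors and reads naturally as the univariate step before the Cox model. The sentence on patients with and without an SA names no test and may be descriptive.

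A reader might also infer that the 5 % error rate is wrong as planned. It is not shown to be: no passage lets any one significant result count as success, and each test alone holds its level. In these simulations the covariate screen itself did not visibly inflate error (Cox 4.9-5.4 %). Nor can a reported risk difference be called wrong, since none is planned. That lost patients would count as free of recurrence is likewise inferred. The article says they are censored, but censoring has no counterpart in a two-by-two table, and the intention-to-treat rule covers all randomised patients.

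Unequal loss is an assumption too. The article gives 10 % without splitting it by arm. The Randomisation section names dropout in the group without SMS as a risk, but says that the Zelen design was chosen to limit it.

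Finally, the covariate list can be left to an analysis plan that is not shown. But the article does not leave it open: it states a data-driven rule and an unranked second comparison, and both can be improved.

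**Conclusion.** The point holds in limited form. Cox is the evident primary method, but its covariates come from the data, and an unranked comparison of the same event between the same groups stands beside it.

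The consequences are conditional. The type I error is about 7.5-8 % only if any significant group result could be claimed, and it stays near 5 % if one test is named. The crude-proportion bias arises only if the comparison is done without regard to follow-up time. It is about 0.4 points with equal 10 % loss. It takes the difference from about 9 to 6.6-7.4 points under an assumed 15 % / 5 % loss, against MEDIA. With that loss reversed, the bias would favour MEDIA. These figures assume constant event hazards, loss unrelated to risk, and 30 % control recurrence at 12 months.

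**What to change.** In Primary outcome analysis:

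1. State that the group hazard ratio from one Cox model, with covariates fixed in advance (for example sex, CES-D at inclusion and centre), is the sole confirmatory test. Keep the p < 0.2 screen, if wanted, for the separate search for risk factors.
2. Label any log-rank test of group as supportive.
3. Replace the comparison of patients with and without an SA by Kaplan-Meier 12-month risks in each group, with 95 % CI, so that the stated censoring is respected.

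This changes wording only and needs no extra data or patients. According to Ethics and permissions, inclusion had not begun when the article was written, so the choice could be fixed before any outcome was seen.
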